#### Primary outcome measure

Positive mental health is the primary outcome. It is measured using the Dutch Mental Health Continuum – Short Form (MHC-SF)
[41]. The MHC-SF is a 14-item questionnaire that measures three core dimensions of positive mental health
[52], which match the three dimensions of the definition of the World Health Organization from 2005
[9]:

• emotional well-being (3 items), defined in terms of the experience of positive feelings and satisfaction with life;

• social well-being (5 items), defined in terms of the self-report of positive functioning in community life (being of social value);

• psychological well-being (6 items), defined in terms of the self-report of positive functioning in individual life (self-realization).

Participants are asked to rate the frequency of feelings they have experienced in the past month. Items are scored on a six-point scale ranging from ‘never’ to ‘every day’. A higher score means more well-being.

Following classical test theory, the three subscales have been found in exploratory and confirmatory factor analyses. The internal consistency, concurrent and discriminant validity of the instrument and its subscales is good. The instrument has satisfactory test-retest reliability, indicating that it is sensitive to change. This is also supported by recent intervention studies
[53,54]. A recent analysis based on item response theory shows that the reliability of the individual items is high across demographics, physical and mental health status, as well as across time
[55]. A pilot study suggested that there would be no interpretation problems caused by this questionnaire in the target group
[24].

#### Secondary outcome measures

1. Loneliness

Loneliness is measured using the eleven-item loneliness scale developed by De Jong Gierveld and Van Tilburg
[38]. Loneliness is measured as the subjectively experienced lack of embeddedness in social relations. The experience of loneliness is an inclusion criterion for the study. The intervention targets socially isolated people and aims to ‘nudge’ them out of their isolation. Loneliness is measured to assess if this aim is reached at the level of subjective experiences.

2. Depression

To measure if candidates decrease in depressive symptoms, the Dutch version of the Center for Epidemiological Studies-Depression Scale (CES-D)
[42,43] is used. It is also used to test the exclusion criterion that a candidate may not have an untreated serious depression.

3. Consumption of care

Using items from the TIC-P (Trimbos/iMTA questionnaire for Costs associated with Psychiatric Illness)
[56], we can assess our hypothesis that the self-reported consumption of care reduces after participating in the Happiness Route. As the outcomes are still self-reported, Vektis, the Dutch information center for care, will carry out analyses on the actual differences in the use of healthcare between the experimental and control group, both before and after the intervention.

4. Purpose in Life

The Purpose in Life Scale
[57,58] measures “the feeling that there is a purpose and meaning in life, (…) a clear comprehensibility of life’s purpose, a sense of directedness, and intentionality”
[57]. The Happiness Route aims to help participants find a (new) aim and purpose in their lives.

5. Resilience

Resilience is measured using the Brief Resilience Scale
[59]. We hypothesize that people who follow the Happiness Route will develop greater resilience. Resilience is often seen as an important individual resource for mental health, especially in difficult situations.

6. Social participation

We measure social participation using items that assess paid or voluntary work, social contacts and activities outside the house. The items are derived from validated national survey studies. The items measure whether the aim of the Happiness Route to nudge people into more social participation is reached.

7. Health-related quality of life

The Dutch version of the EuroQol (EQ-5D)
[40] is used to measure if participants will have an improved health-related quality of life after following the Happiness Route. It is also used as an inclusion instrument for assessing whether or not participants have health limitations.

#### Moderating measures

To address the question whether the effect of the intervention is different for participants with varying backgrounds, we will examine whether age, gender, and cultural background moderate the effectiveness of the intervention. To address the question whether the effect of the intervention depends on the characteristics of counselors, we will examine the moderating effects of the characteristics of counselors: work experience, work satisfaction, and adherence. For *work experience* we will compute an index that is based on educational level and number of years’ experience. For *work satisfaction*, we will compute an index that is based on work engagement
[49] and job satisfaction
[50,51]. Furthermore, counselors will fill out online logs for each participant after every home visit. These logs can be used to measure *adherence*.

### Statistical analyses

#### Descriptive statistics

A CONSORT flow chart of participation during the total study will be drawn. Reasons for drop-out will be summarized. Percentages of missing values and dropout will be displayed. The evaluation interviews with counselors and participants will be subject to a content analysis and the descriptive statistics of the categories resulting from this content analysis will be computed.

#### Univariate analyses

Univariate analyses on the differences between the intervention and control groups at baseline (chi-square and t-tests) will be performed to check whether the randomization has succeeded.

#### Multivariate analyses

We will first do a missing data analysis for all participants on the second and third measurement point. A logistic regression analysis will be conducted with having complete data as the dependent variable, and demographic and psychosocial characteristics at baseline measurement as independent variables to assess non-random missings. We will use multiple imputations (five data sets) to replace missing values and carry out the analyses on the pooled data set. Hence, all participants who were randomized can be included in the statistical analyses. The results from this imputed intention-to-treat sample will be compared to the results of the observed data only.

We will use MANOVA analyses to assess the effectiveness of the intervention in reaching its primary and secondary outcomes. The measures at baseline, post-treatment, and follow-up are repeated measures and the experimental condition versus the control condition is the independent variable. In all analyses, we take into account that the observations are clustered as participants are ‘nested’ in each of the ten local institutions. Therefore, robust standard errors are computed using the first-order Taylor-series linearization method.

Standardized mean differences (Cohen's d) at post-intervention and follow-up are calculated as the difference between the means of the treatment and control condition divided by the standard error of the control condition. We expect a small to moderate effect size for the primary outcome (Cohen’s d= 0.35).

To answer the question on moderating participant factors, we will analyze the moderating effects of demographic characteristics (age, gender, and cultural background) on the effectiveness of the intervention. Following Kraemer et al.
[60], we will enter the change score of positive mental health at nine months minus baseline as a dependent variable in a linear regression model. The condition dummy (experimental versus control condition), the potential moderator, and their interaction are independent variables. When the interaction effect is significant, there is a differential effect of the intervention for this particular moderator. Analyses will be carried out for each of the three potential moderator variables separately.

We do similar regression analyses to answer the question on moderating counselor factors. The potential moderators are the indices for work experience, work satisfaction, and adherence to the program as measured with the questionnaire for counselors and the logs of the counselors.

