### Power calculation and sample size

Based on a meta-analysis of previous studies in positive psychology, conducted with instruments that are similar to the MHC-SF
[27], we expect a small to medium effect size for the intervention Happiness Route (Cohen’s d = 0.35). A pilot study
[25] and experiences from previous practice showed that there are no negative effects on the well-being of participants. We therefore specified a one-tailed test with an alpha level of 0.05 under the assumption that the Happiness Route will be more effective than the Customized Care group, as the latter is not intended to improve positive mental health. This has also been shown in previous studies on positive psychological interventions
[27]. Given ethical considerations, Knottnerus and Bouter
[61] argued that one-sided testing is preferable under these circumstances. Power analysis with the program GPower with a power of 0.80 (1 – beta of 0.20), indicates that 102 participants are needed in each condition. We used a maximal drop-out rate of 20% which is a conservative estimate from previous experience. In everyday practice, the drop-out was about 10% of the more than 500 people who already participated in a Happiness Route. With a maximal drop-out of 20%, we need 128 participants in each condition, 256 in total.

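### Five imputed data sets leave a near-threshold intention-to-treat result dependent on the random seed; more imputations would be an almost free, minor improvement

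*Protocol article*

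**What the plan says.** The Multivariate analyses section of the protocol article fixes the number of imputations: "We will use multiple imputations (five data sets) to replace missing values". All randomised participants are thereby kept in the analysis, and a comparison is promised: "The results from this imputed intention-to-treat sample will be compared to the results of the observed data only". The article gives no reason for choosing five and mentions no check on Monte Carlo error.

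The section Power calculation and sample size sets the context. The test is one-sided ("We therefore specified a one-tailed test with an alpha level of 0.05") and the trial is sized "with a power of 0.80". On missing data it says: "We used a maximal drop-out rate of 20% which is a conservative estimate from previous experience". It adds that drop-out among people who had already followed the Happiness Route was about 10%. The resulting size is: "With a maximal drop-out of 20%, we need 128 participants in each condition, 256 in total".

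**The concern.** Multiple imputation draws the missing values at random, so the pooled estimate and its p-value depend on the seed. That dependence shrinks as the number of imputations m grows. With m = 5 and up to one fifth of the outcomes missing, it may be large enough for two analysts with the same data, model and code to fall on opposite sides of 0.05.

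The imputed sample carries the intention-to-treat claim, which the Discussion presents as a strength over earlier studies. A verdict that moves with the seed is hard to defend, and without a seed fixed in advance it leaves room to choose among runs. The same noise enters the imputed analyses of the seven secondary outcomes. It also adds a spurious element to the comparison of imputed with observed-only results.

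**Working it through.** **Inputs from the protocol article.** m = 5; drop-out at most 20%, about 10% in practice; one-sided alpha 0.05; power 0.80; d = 0.35; 102 evaluable and 128 randomised per arm.

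**Assumptions not in the article.** Outcomes missing completely at random; one follow-up time point; baseline-outcome correlation of 0, 0.5 or 0.7; no site clustering; the imputed sets analysed separately and combined by Rubin's rules. The fraction of missing information (FMI) is taken as close to the missing fraction; the simulation gave 0.103 at 10% missing and about 0.205 at 20%.

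**1. The plan's own figure.** The normal approximation 2(1.645 + 0.842)² / 0.35² gives about 101 per arm. The exact one-sided t-test gives 101.6, hence 102. Inflating, 102 / 0.80 = 127.5, hence 128 per arm and 256 in total. The stated figures are reproduced.

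**2. Rubin's-rule quantities at FMI = 0.20, m = 5.**
- Relative efficiency: 1 / (1 + FMI/m) = 1 / 1.04 = 0.962.
- Inflation of the standard error: √1.04 = 1.020, or 2%.
- Seed-to-seed SD of the estimate, in units of its standard error: √(FMI/m) = √(0.20/5) = 0.20. It is 0.10 at m = 20, 0.063 at m = 50 and 0.045 at m = 100.
- At FMI = 0.10 and m = 5: √(0.10/5) = 0.14.

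**3. Whole-trial simulation.** N = 256, d = 0.35, baseline-adjusted treatment effect, one-sided 0.05, 1,500 trials per scenario. Each trial was imputed twice independently. The table gives the share of trials in which the two runs disagreed on significance.

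| Missing | m | corr. 0 | corr. 0.5 | corr. 0.7 |
|---|---|---|---|---|
| 20% | 5 | 10.1% | 6.4% | 2.3% |
| 20% | 20 | 4.1% | 3.4% | 0.9% |
| 20% | 50 | 2.7% | 1.5% | 0.6% |
| 20% | 100 | 1.9% | 1.0% | 0.3% |
| 10% | 5 | 4.3% | 2.7% | 1.0% |

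With no true effect and 20% missing, type I error at m = 5 was 0.049 to 0.051. Power at m = 5 against m = 100 was 0.769 against 0.792, 0.880 against 0.895, and 0.968 against 0.976 for the three correlations.

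**4. One fixed data set, re-imputed repeatedly (20% missing, m = 5, correlations 0 and 0.5).**

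| p with many imputations | 95% range of p at m = 5 | runs with p above 0.05 |
|---|---|---|
| 0.03 | 0.010 to 0.09 | about 22% |
| 0.02 | 0.006 to 0.07 | 8 to 11% |
| 0.01 | 0.002 to 0.04 | about 1% |
| 0.005 | 0.001 to 0.03 | at most 0.3% |

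At m = 50, a data set with p about 0.03 was non-significant in 0.1% of runs.

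**5. How often the trial lands near the limit.** With 102 per arm the expected z is 0.35 × √(102/2) = 2.50. A one-sided p between 0.02 and 0.10 corresponds to z between 1.28 and 2.05. The probability is Φ(2.05 − 2.50) − Φ(1.28 − 2.50) = Φ(−0.45) − Φ(−1.22), about 0.22.

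**The case against.** The case for leaving the plan alone is substantial. Five imputations give valid and nearly efficient inference. The expected z of 2.50 corresponds to p of about 0.006, where the verdict flips in about 1% of runs or fewer. The 20% figure is a ceiling that the article itself calls conservative; at 10% missing, disagreement is less than half as large. The observed-data analysis involves no seed and will stand beside the imputed one. For participants who return the three-month but not the nine-month questionnaire, the three-month score could lower the missing information below what was simulated. High flip rates arise only by conditioning: in data chosen to have an observed-case z of 1.80, 34% of seeds missed p < 0.05, but that describes a borderline data set and not this trial.

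Most of this stands and limits the point to a minor one. Two parts are weaker. The 10% describes people in the Happiness Route in everyday practice. It does not describe the control arm, or the return of questionnaires mailed at three and nine months. And the observed-data comparison does not make the imputed result itself reproducible.

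**Conclusion.** The point holds as a minor one about reproducibility. At the planned maximum of 20% missing, seed noise is about 0.20 of the standard error, and a result with p of roughly 0.02 or above can cross the one-tailed 0.05 limit with the seed. Two runs disagree in about 2 to 10% of trials at 20% missing and about 1 to 4% at 10%. Fifty imputations cut the 20% figure roughly fourfold. No finite m removes the dependence for a result lying exactly at the limit. These sizes rest on the assumptions listed with the working, above all the baseline-outcome correlation.

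Three stronger readings are tempting but unsupported:
- A reader might infer that five imputations make the intention-to-treat analysis invalid. The type I error and efficiency figures show otherwise.
- A reader might infer that the noise mainly costs the trial a significant result. It runs both ways, and a non-significant result can equally become significant.
- The article also plans moderator tests ("We do similar regression analyses to answer the question on moderating counselor factors"), so a reader might infer that imputation will shrink the condition-by-moderator interactions toward zero. That would follow from an imputation model without interaction terms, but the article does not describe its imputation model, and that detail may properly sit in the analysis plan.

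**What to change.** In the Multivariate analyses section, replace five with at least 50 imputed data sets. State that each set is analysed separately and the results combined by Rubin's rules, set the seed before the analysis, and report the Monte Carlo error of the pooled estimate and p-value.

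The cost is minutes of computing. What is estimated does not change, and no additional data are needed.

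This point gives no ground for requiring imputation separately within each condition. That would leave about 102 completers per arm behind each imputation model at 20% drop-out, with eight outcomes measured three times to accommodate, so it is a trade-off and not a free change.

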## Abstract

**Background:**

The Happiness Route is an innovative intervention that uses a happiness-based approach for people with an accumulation of risk factors for low well-being: socially isolated people with health impairments and a low socioeconomic status. The goal of this intervention is to improve well-being by engaging participants in intrinsically motivated activities with methods from positive psychology. We hypothesize that the primary outcome measure, emotional, social and psychological well-being of participants of the Happiness Route, will increase in comparison to the traditional and commonly-used problem-based approach. Secondary outcome measures are health-related quality of life, psychosocial functioning and health care consumption.

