**Methods and design:**

Participants will be socially isolated people with health problems and a low socioeconomic status. Participants will be recruited in ten Dutch communities and candidates will be signed up by intermediaries, professionals from the health and social sector. Randomly assigned, half of the participants will follow the Happiness Route and half of the participants will follow the active, problem-focused control group ‘Customized Care’. In total, 256 participants will be included. In both conditions, participants will receive counseling sessions from trained counselors. In the control group, participants will talk about their problems and the care they get and counselors help to optimize their care. In the Happiness Route, the counselor ask questions such as “How do you want to live your life?”. The intervention helps people to find their ‘passion’, i.e., a positive goal-engaged and intrinsically motivated activity. It enables them to follow their passion through by a once-only personal happiness budget (maximal €500). We use well-validated and reliable questionnaires to measure primary and secondary outcome measures at baseline, directly after the intervention and at a nine-month follow-up.

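### Baseline MHC-SF is analysed as an outcome, with no deciding term or primary time point named, while the trial is sized on one one-tailed contrast; a baseline-adjusted 1-df test would match the sizing

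*Protocol article*

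**What the plan says.** Under Statistical analyses, Multivariate analyses, the protocol article chooses MANOVA for the primary and secondary outcomes and sets it up as follows: "The measures at baseline, post-treatment, and follow-up are repeated measures and the experimental condition versus the control condition is the independent variable". No condition-by-time term is mentioned. Cohen's d is to be reported at both later measurements, and neither is ranked first. Nine months is singled out only for the moderator question, where "we will enter the change score of positive mental health at nine months minus baseline as a dependent variable in a linear regression model".

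The Abstract describes "the primary outcome measure, emotional, social and psychological well-being of participants of the Happiness Route". The Primary outcome measure section names one construct, positive mental health, and one instrument, the MHC-SF, with three dimensions. It does not say in words that the effect test uses the total score.

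The Power calculation and sample size section is framed differently: "We therefore specified a one-tailed test with an alpha level of 0.05". With d = 0.35 and power 0.80 it "indicates that 102 participants are needed in each condition". The d of 0.35 is not attached to three or to nine months.

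**The concern.** Baseline is measured before randomization, so the true difference between conditions at that wave is zero. Treating it as a dependent variable makes the result depend on which term of the model is read. The condition main effect averages the null wave in with the two informative ones. The condition-by-time effect does not, but it is a 2-df test without direction. Neither is the single directional comparison that justified 256 participants.

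Two things are at stake. The first is power: a strong predictor of the outcome is collected on everyone and is not used as a covariate. The second is the claim itself: with no primary time point fixed, it is open whether three months, nine months or both must show an effect.

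**Working it through.** **Inputs from the article.** d = 0.35 on an SD = 1 scale, one-sided alpha 0.05, power 0.80, 1:1 allocation, 102 evaluable per condition, 20% drop-out, three waves (baseline, three and nine months).

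**Assumptions, not in the article.** Equal variances; the same correlation rho between any two waves (compound symmetry), taken over 0.3 to 0.8; true effect 0 at baseline and 0.35 at both later waves; no allowance for site clustering.

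**1. The plan's own figure.** The normal approximation gives 101 per condition. The exact noncentral t gives power 0.798 at 101 and 0.801 at 102, so 102 is reproduced. 102 / 0.80 = 127.5, rounded up to 128 per condition, 256 in total. A two-sided test would need 129 evaluable per condition by the normal approximation. The stated figure is therefore a one-sided t-test on one score at one time, with no repeated measures and no baseline term.

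**2. If the condition main effect decides.**
- Raw contrast: (0 + 0.35 + 0.35) / 3 = 0.233.
- SD of the three-wave mean: sqrt((1 + 2 rho) / 3).
- Standardized effect: 0.233 divided by that SD. Power comes from the noncentral t with 202 df and noncentrality equal to the effect times sqrt(102 / 2).

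**3. If condition-by-time decides.**
- The two changes from baseline each have mean difference 0.35, variance 2(1 - rho) and covariance 1 - rho.
- Noncentrality: (102 / 2) x 2 x 0.35² / (3(1 - rho)) = 4.165 / (1 - rho), which is 5.95, 8.33, 13.88 and 20.83 at the four correlations below.
- Power comes from the noncentral F with 2 and 201 df at alpha 0.05.

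**4. Condition effect at one time point with baseline as covariate.**
- Standardized effect: 0.35 / sqrt(1 - rho²), which is 0.367, 0.404, 0.490 and 0.583.
- Power comes from the noncentral t as in step 2.

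| Power at 102 per condition | rho 0.3 | rho 0.5 | rho 0.7 | rho 0.8 |
|---|---|---|---|---|
| Main effect: standardized effect | 0.320 | 0.286 | 0.261 | 0.251 |
| Main effect, one-sided 0.05 | 0.74 | 0.65 | 0.58 | 0.56 |
| Condition-by-time, 2 df, 0.05 | 0.57 | 0.73 | 0.92 | 0.99 |
| Baseline as covariate, one-sided 0.05 | 0.83 | 0.89 | 0.97 | 0.99 |
| Baseline as covariate, two-sided 0.05 | 0.74 | 0.82 | 0.94 | 0.99 |

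The two-sided row allows a like-for-like comparison with the non-directional 2-df test. It shows that part of the gap over condition-by-time comes from sidedness, and that the rest shrinks to nothing by rho 0.8.

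**5. Two candidate time points.** If success at either wave counted, each at one-sided 0.05, the error would be 1 - 0.95² = 0.0975 under independence. For correlated waves it is 0.093, 0.088, 0.080 and 0.075 at correlations 0.3, 0.5, 0.7 and 0.8.

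**6. Moderator regressions.** The change score has variance 2(1 - rho), and the baseline-adjusted residual has 1 - rho². Their ratio is (1 + rho) / 2, or 0.65, 0.75, 0.85 and 0.90 at the four correlations. The change score is valid but less precise.

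**The case against.** The best defence is that the quoted sentence describes the layout and does not name the test. The hypothesis is that well-being rises relative to the control approach, which in a repeated-measures design corresponds to condition-by-time. That test is valid, and under the assumptions above it exceeds the planned 0.80 at rho 0.7 and 0.8. A joint multivariate test of all three waves is another possible reading. It also avoids averaging, with power 0.80, 0.85, 0.95 and 0.99, but it too has no direction. A separate analysis plan, not shown, could name the deciding term. All of this stands. A reader might infer that the planned test is diluted as a matter of fact, and the article does not support that: dilution follows only if the main effect decides.

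A reader might also infer that no primary score exists, or that success on any subscale or at either time would count. The article does not say so. Table 1 has one primary row, the exclusion criterion applies one overall MHC-SF cut-off (4.83), and the moderator model uses one positive mental health score. No separate subscale tests are planned. Giving Cohen's d at two times is reporting, not a decision rule, and an omnibus test used as a gate would limit any inflation.

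The defence does not remove the mismatch. The article itself places baseline among the outcomes and itself specifies a one-tailed single comparison for the sample size. None of these readings of the model is that comparison.

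**Conclusion.** The point holds in limited form. The effectiveness model and the sample size calculation describe different tests, and the article does not say which term or which time point decides. If the main effect decides, one-sided power falls below the planned 0.80 at every correlation tried (0.74 down to 0.56). If condition-by-time decides, there is no dilution, but power ranges from 0.57 to 0.99 and the test is not one-tailed. A baseline-adjusted contrast fits the calculation and gives 0.83 to 0.99.

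These figures rest on compound symmetry, equal effects at both follow-ups and no site clustering; the correlations are assumed. The one-sided error of about 0.08 to 0.09 for two time points is a risk left open, not a rule the plan states. The moderator regressions are not wrong.

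**What to change.** Make the primary analysis a linear regression or mixed model of total MHC-SF at one named time point on condition, with baseline MHC-SF as covariate. Test condition as a 1-df effect at the stated alpha and sidedness. Nine months is the natural choice, since the moderator analysis already uses it. The other time point and the three subscales become secondary. If MANOVA is kept, state which term decides, and at what alpha and sidedness. Baseline as covariate in the moderator regressions is an optional gain in precision.

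The cost is wording only. Baseline MHC-SF is already collected before randomization, so no extra data or participants are needed. With nine months as primary, the three-month result can no longer carry the primary claim. The choice should be recorded before outcome data are seen.

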### Setting

The study will be carried out in the field of healthcare and social work in nine municipalities in the Netherlands by the University of Twente and Arcon, an organization in the welfare sector. The study is funded by ZonMw (the Netherlands Organisation for Health Research and Development) under the prevention program. A municipal officer will generally be the local project leader, but in some cases, the local project leader works in one of the participating institutions. The local project leader is responsible for the recruitment through intermediaries, the allocation of participants to counselors and for the final approval on spending the budget in the Happiness Route. Municipalities mostly provide financial support for the training of counselors, the appointment of the local project leader, as well as the budget for the Happiness Routes. In other cases, the project is financed by social funds.

The recruitment of participants will be carried out by intermediaries who work as professionals in local care and social work institutions. Examples of intermediary organizations and professions are home care, housing associations, after-care nurses, psychiatric nurses, religious institutions, well-being institutions and organizations for people with mental disabilities. Intermediaries are in direct contact with the target group in their daily work. They can suggest possible candidates to the local project leader, who informed the intermediaries about the study and the target group.

Counselors are experienced professionals, such as social workers, and in some cases experienced volunteers. They are responsible for the intake and the delivery of the experimental and control interventions. To avoid contamination between the experimental and the control conditions, counselors will only deliver interventions in one of these conditions. Both counselors providing the Happiness Route and counselors providing the control condition will receive suitable training.

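### The sample size assumes independent participants, while the analysis is cluster-adjusted on nine or ten sites and counselors work in one arm only, so the stated power of 0.80 may be too high

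*Protocol article*

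**What the plan says.** - **Sample size** (Power calculation and sample size). The inputs are the expected effect ("we expect a small to medium effect size for the intervention Happiness Route (Cohen’s d = 0.35"), a "one-tailed test with an alpha level of 0.05" and the target power ("Power analysis with the program GPower with a power of 0.80"). The section concludes that the calculation "indicates that 102 participants are needed in each condition", and raises this to 128 per arm (256 in total) for a maximal drop-out of 20%. It gives no intraclass correlation (ICC), cluster size or design effect.
- **Analysis** (Multivariate analyses). All analyses are to allow for participants being nested "in each of the ten local institutions". The method is: "Therefore, robust standard errors are computed using the first-order Taylor-series linearization method". No counselor-level term is named.
- **Number of sites.** The Abstract and Multivariate analyses count ten. The Setting section places the study "in nine municipalities in the Netherlands".
- **Counselors** (Setting). To avoid contamination, "counselors will only deliver interventions in one of these conditions".
- **Randomization.** Participants are randomized individually from a computer-generated list, without stratification.

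**The concern.** The power statement and the analysis describe different tests. The power figure treats all participants as independent; the analysis says that they are not.

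The level of clustering matters too. Sites contain both arms, so a site effect mostly drops out of the difference between arms. A counselor effect does not, because each counselor contributes to one arm only. Counselors run every session in both conditions, and participants may ask them for help with the outcome questionnaires, so correlation within a counselor's caseload is plausible. The article itself plans to test counselor experience, satisfaction and adherence as moderators.

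First-order linearization is a large-sample method, and here it rests on nine or ten clusters. Two things are at stake: whether the primary test keeps its 5% level, and whether 256 participants deliver the stated power. A null result from an underpowered trial could wrongly count against the intervention.

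**Working it through.** **1. Reproduce the plan's figure.** With d = 0.35, one-sided alpha 0.05 and power 0.80, the two-sample t-test needs 101.6 per arm, so 102. Power at 102 is 0.801. Drop-out: 102 / (1 − 0.20) = 127.5, so 128 per arm and 256 in total. The stated numbers reproduce exactly with independent observations, so they contain no allowance for clustering.

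**2. Few clusters, no counselor effect.** The noncentrality is d × √(n/2) = 0.35 × √51 = 2.50. A t reference on G − 1 df, with G the number of sites, gives:

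| Sites (G) | df | Critical value | Power at 102 per arm |
|---|---|---|---|
| 9 | 8 | 1.860 | 0.738 |
| 10 | 9 | 1.833 | 0.746 |

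If 1.645 (normal) is used instead, the one-sided tail area is 0.069 on 8 df and 0.067 on 9 df.

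Simulation supports this: 204 analysed, 9 or 10 sites, equal and unequal sizes, two counselors per site and arm, site-clustered errors, 4,000 runs per cell. Across all cells, one-sided type I error was 0.066 to 0.078 with the normal reference and 0.047 to 0.059 with t on G − 1 df. With no counselor effect, power with the t reference was 0.74 to 0.76.

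**3. Site clustering alone.** With a site ICC of 0.05 (assumed) and no counselor effect, the ordinary unclustered test kept power of about 0.80 in the simulation. Site correlation itself costs little.

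**4. Counselor clustering, ordinary df.** The article gives neither the ICC nor the caseload m, so both are assumed. The design effect is DE = 1 + (m − 1) × ICC. Power is the normal approximation Φ(0.35 × √(102/DE/2) − 1.645). Enrolment to restore 0.80 is 102 × DE, rounded up, then divided by 0.80 and rounded up.

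| m | ICC | DE | Power | Enrolled per arm |
|---|---|---|---|---|
| 2 | 0.01 | 1.01 | 0.80 | 130 |
| 5 | 0.01 | 1.04 | 0.79 | 134 |
| 5 | 0.05 | 1.20 | 0.74 | 154 |
| 5 | 0.10 | 1.40 | 0.68 | 179 |
| 10 | 0.01 | 1.09 | 0.77 | 140 |
| 10 | 0.05 | 1.45 | 0.67 | 185 |
| 10 | 0.10 | 1.90 | 0.57 | 243 |

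The plan enrols 128 per arm.

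**5. Both together.** In the simulation with counselor ICC 0.05 (mean caseload about 5, since 204 / (10 × 2 × 2) = 5.1), the t reference gave power of 0.65 to 0.67.

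**6. Possible offsets.**
- *Baseline information.* The power calculation uses none, but the analysis is of repeated measures. A baseline-to-follow-up contrast has variance factor 2(1 − r), a gain only if the correlation r exceeds 0.5. With r = 0.6 (assumed) the factor is 0.8. Power is then about 0.82 for m = 5 and ICC 0.05 on ordinary df, taking that ICC to hold for change scores. With t on 9 df and no counselor effect it is also about 0.82.
- *Drop-out.* The article reports about 10% in practice: 128 × 0.90 is about 115 per arm. With m = 5 and ICC 0.02, power is about 0.82. With t on 9 df and no counselor effect it is 0.79.

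**The case against.** **Power is not shown to be overstated.** The ICC and caseload are assumptions. At caseload 2 and ICC 0.01 the loss is negligible, and a baseline correlation above 0.5 or drop-out nearer 10% could recover some or all of it. This stands, and it limits the conclusion to a conditional one. It does not rescue the stated calculation, which claims no baseline gain and plans on 20% drop-out.

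**A reader might infer that the standard errors are unreliable.** The article does not support that. If each counselor works in one site (an assumption), errors clustered on site also absorb counselor correlation, and a t reference on G − 1 df brings type I error close to nominal. The inflation to about 0.07 arises only with a normal reference, which the article never states. A fuller analysis plan may settle the reference distribution, so its absence here is not an error.

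**A reader might also infer that MANOVA and robust errors cannot be combined.** Standard MANOVA F tests do not use linearized errors, but the same contrasts can be tested by Wald tests with a robust covariance. The text need only say which test gives the primary p-value.

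**The choice of model is partly preference.** Agreed. Site-clustered errors with a small-sample correction are an acceptable alternative to a mixed model.

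**Conclusion.** The concern holds in a limited form and should be fixed; it does not invalidate the design. Three things follow from the article alone: the sample size is that of an unclustered test, counselors are nested within arm without any allowance for it, and the site count is given as both nine and ten.

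Under the plan's own inputs, a site-clustered test with a t reference has power of about 0.74 to 0.75 at 102 per arm, not 0.80, before any counselor effect. The further loss from counselors cannot be sized from the article. On ordinary df it brings power to between 0.80 and about 0.57 over the assumed ranges (ICC 0.01 to 0.10, caseload 2 to 10). Because the offsets are real but unquantified, the right statement is that power may be overstated, not that it certainly is.

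**What to change.** 1. For the primary contrast, choose one of two methods and say which test gives the primary p-value:
   - a mixed model with site as a fixed effect, a random counselor intercept and small-sample df (Satterthwaite or Kenward-Roger); or
   - site-clustered robust errors with a bias-reduced correction and t df.
2. Reconcile nine and ten sites, since the count sets the degrees of freedom.
3. Restate power at N = 256 over a stated range of counselor ICC and caseload. If a gain from baseline correlation is claimed, state the correlation assumed.

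The cost is small: revised wording, and a counselor identifier kept with each participant's data, which the session logs should already carry. The downside is a somewhat wider interval and a lower stated power.
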